3.4.1.2 Estimation of the VES-13 reproducibility

The test-retest reproducibility study for the VES-13 questionnaire will be performed on a sample of patients from the Oncodage study. Pearson’s reproducibility coefficient after one month for the English VES-13 in a population of patients over 70 treated by anti-androgens for a prostatic cancer (Mohile et al., 2007) was 0.92 overall (respectively 0.52, 0.60, and 0.70 for the subsets concerning health perception, physical and functional disabilities) but data for the intraclass correlation coefficient were not found in the literature for the VES-13 test-retest assessment.

For two measures, the inclusion of 160 patients would provide an estimation for the intraclass correlation coefficient of 0.6 with an accuracy corresponding to a 95% CI of 0.2 width, *i.e.* 95% CI = [0,5-0,7] (Bonett, 2002).The accuracy obtained will be even better if the obtained coefficient is higher.

In order to be sure of getting 160 patients assessed by the VES-13 at both times (oncologic consultation and geriatric assessment), it has been decided to included 180 patients, corresponding to the first 60 patients who will be included in the three participating centres (Bordeaux, Lille, Lyons).

**3.4.2 Study population**

The main analysis, the validation of the screening tool, will be conducted on every patient included in the study.

Secondly, the new screening tool will also be assessed according to:

- the type of cancer,
- the stage of the cancer (local/metastasis),
- the therapeutic strategy (according to three groups: locoregional treatment, locoregional and adjuvant treatment, general treatment).

**3.4.3 Statistical analysis**

The population of the study will be described broadly according to its clinical and sociodemographic characteristics in terms of size and ratio for the qualitative variables and in terms of distribution for the quantitative ones.

Missing data will be reported (by item and by questionnaire) thanks to frequency and percentage. The reasons for these missing data for any test will be described.

The following parameters will be estimated:

- **The sensitivity** will be estimated with the proportion of patients registered as “requiring a geriatric intervention” by the new tool, among the patients having at least one abnormal CGA element. A 95% CI will be reported (binomial distribution).
- **The specificity** will be estimated with the proportion of patients registered as “not requiring a geriatric intervention” by the new tool, among the patients having no abnormal CGA element.

A 95% CI will be reported (binomial distribution).

- **The positive predictive value** will be estimated with the proportion of patients having at least one abnormal CGA element, among the patients registered as “requiring a geriatric intervention” by the new tool. A 95% CI will be reported.
- **The negative predictive value** will be estimated with the proportion of patients having no abnormal CGA element, among the patients registered as “not requiring a geriatric intervention” by the new tool. A 95% CI will be reported (binomial distribution).
- **The ROC curve** representing graphically the sensitivity according to the (1 -specificity) for various thresholds of the assessed test will be represented graphically and help determine the area under the curve (AUC).
- **The internal consistency** will be assessed according to Cronbach’s alpha coefficient (Armitage & Berry, 2002).A 95% CI will be reported.
- **The reproducibility** will be assessed by the intraclass correlation coefficient for quantitative variables, with a 95% CI.
- **Scores between acknowledged subgroups** will be compared thanks to a variance analysis.
- **The area under the ROC curve** for G8 and VES-13 will be compared (Hanley et al, 1983).
- **We will assess whether using both screening tools together** (G8 and VES-13) helps obtaining a more effective screening tool compared to the sole use of one questionnaire (Macaskill et al., 2002).
- **Biological data** will be described thanks to descriptive statistics for overall population and then by localisation. We will thus assess whether inclusion of these variables (individually or simultaneously) in the new screening tool participates in the improvement of the tool’s achievements. We will study the screening tool’s sensitivity and specificity when it takes into account these biological data.
- **For the prognostic analysis** (predictive validity study), delays will be calculated between the origin date (inclusion in the study) and the event date (death, progression, or institutionalisation). Survival curves will be represented graphically with Kaplan-Meier’s method (Kaplan et al. 1958). Median times for survival will be reported with a 95% CI. Patients will be compared according to the categories defined by the G8 and VES-13 thresholds determined by the analysis of the corresponding objectives of our study, thanks to a Log-Rank test, if application conditions are respected. A Cox regression model (Cox, 1972) will enable us to determine the relative risks (RR) (and their CI) associated to VES-13 and G8 initial results for the occurrence of various events of interest (death and institutionalisation), taking into account the durations. A stratified analysis on the various prognostic factors (independent from CGA) will be performed: such as type of cancer, or initial grade. The analysis of the “institutionalisation” risk will be only on the patients not institutionalised at the inclusion (population at risk).
- **Regarding the particular case of** **MMSE,** secondary analyses for robustness will be performed using different thresholds to define an altered MMSE, taking into account the score distribution according to the education level and the age.

All the analyses will be performed with the SAS 9.1. software, with a type I error of 5%.

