Appendix S2 – ONCODAGE study protocol (abridged translation from French)

| **Study title** | Validation of a geriatric screening tool in oncology |
| --- | --- |
| **Acronym** | **ONCODAGE** |
| **Coordinating centre** | Institut Bergonié, Centre de Lutte Contre le Cancer, Bordeaux. |
| **Coordinator** | Pr. [name] |
| **Number of centres** | At least 15: the 15 Pilot Units of Coordination in Geriatric Oncology (*UPCOG*) along with health institutions members of the oncology network. |
| **Indication** | Patients over 70 years old with a cancer (colon, lung, ENT, breast, prostate, lymphoma), as part of the initial management. |
| **Trial rationale** | As patients age, risks for serious toxicity, or even lethality, during cancer treatment increase. A detailed assessment of the patient’s status is required.  Comprehensive geriatric assessment (CGA) is a method which has proved its usefulness but which is time-consuming and expensive to administer. A screening tool allowing the individualisation of patients who would benefit from a CGA is necessary.  In a previous regional prospective multicentre cohort (regional Ministry of Health-financed project, PHRC 2003), we studied patients over 70 years with cancers who were receiving first-line chemotherapy. This study enabled us to perform an exploratory study in order to develop a screening tool, the G8, which consists of a 7-item questionnaire from the Mini Nutritional Assessment (MNA) and an age indication. We applied the suggested screening tool to our population of 364 patients and this analysis provided encouraging results to be studied on a wider scale (Bellera et al., Ann Oncol, 2012). |
| **Expected effects** | With the use of this simple tool for screening, to be administered by nurses or oncologists, we consider that more elderly patients with cancer will be able to benefit from a CGA.  This tool will also enable us to rationalise the use of our geriatric assessment means and thus to focus their use on those who need it more, for more efficacy. |
| **Main objective** | Validate a new screening tool, the G8, to identify within a population of over 70-year-old patients with cancer those who need further geriatric assessment. |

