| **Course of the study** | **Oncological assessment consultation** *(oncologist and nurse)*   - Information leaflet and informed consent, - Assessment of eligibility criteria, - Standard clinical examination (oncologist), - G8 questionnaire (oncologist), - VES-13 self-questionnaire (nurse), - Organisation of appointments for oncological assessment (pre-therapeutic evaluation, extended assessment), and geriatric oncologic assessment.   **Oncological assessment**  The oncological assessment is the extended and standard pre-therapeutic assessments usually performed for patients. Clinical and paraclinical data will be collected for the study.  **Geriatric oncologic assessment** *(geriatrician and geriatric assessment nurse for UPCOG)*  Before starting the oncological treatment and before setting up specific management, within two weeks at least after the oncological assessment consultation.  The nurse (IEG) will have to:   - Filling ADL, IADL, MNA questionnaires, along with the socio-cultural assessment score, - Performing the MMS and Timed Get up and Go tests, - Filling GDS-15 and QLQ- C30 self-questionnaires.   The geriatrician will then receive the patient for an oncological geriatrics consultation and will be in charge of the CIRS-G questionnaire, the synthesis of the self-questionnaires, the oncological geriatrics assessment, and of the clinical file. The doctor will try to recognise the patient for who the setting of a personalised programme of geriatric interventions is required.  **It is essential for the geriatrician not to have access to the G8 nor to the VES-13.**  **Follow-up**  Patients will be followed over 5 years. Data collection will be done at 1 and 5 years in order to collect data on vital status, disease progression, lifestyle (ambulatory, institutionalised). |

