| **Summary of the study course** | **Step 1: Inclusion (J0)**  (Medical oncologists, surgeons, radiotherapists...)  _ Information leaflet  _ Informed consent  _ Inclusion and non-inclusion criteria  _ Inclusion form  **Step 1: Initial oncologic consultation (J0)**  (Medical oncologists, surgeons, radiotherapists...)  _ Booking an appointment for the geriatrics consultation  _ General information on the patient  _ Information on cancer  _ G8 questionnaire  _ VES-13 self-questionnaire  **Step 2: Oncological extended assessment (J0-J30)**  _ Biological data  **Step 3: Geriatrics consultation (J1-J30)**  (Geriatrician and nurse)  _ Geriatric assessment:  _ MMSE  _ ADL, IADL  _ GDS-15  _ QLQ-C30, sociocultural assessment  _ Timed Get up and Go  _ MNA  _ CIRS-G  _ Geriatrician’s recommendations  VES-13 again for 60 patients/centre in three centres:  Bordeaux, Lille and Lyons  **Step 4: Follow-up at 1 and 5 years**  Follow-up data collection (vital status and lifestyle) |

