**3.4 STATISTICAL FACTORS**

**3.4.1 Hypotheses and required number of patients**

3.4.1.1 Main analysis

For a screening tool, sensitivity and specificity are assessed jointly, although we tend to favour sensitivity as it could be damageable not to detect patients requiring a CGA. The objective then is to maximise the sensitivity of the new screening tool.

Our exploratory study suggests (Chapter 9):

a sensitivity of about 90%, when we use as gold standard the presence of an abnormal score for at least one questionnaire,

a prevalence of 50% of patients with at least one abnormal questionnaire.

Supposing that the real sensitivity for our G8 screening tool is 90%, we estimate that the inclusion of 750 patients with at least one abnormal questionnaire would be enough to estimate the sensitivity with a sufficient accuracy (2.4%) and to obtain a 95% CI between 88% and 92%. Supposing that 50% of our population will have at least one abnormal questionnaire, **1500 assessable patients** will be needed.

A patient is said to be assessable if CGA and G8 data are complete. In our exploratory study, only 309 patients out of 364 had all the necessary questionnaires for CGA (85%). In order to ensure a minimum of 1500 assessable patients, we will recruit 1650 patients.

If we want to estimate sensitivity according to the type of cancer, we will obtain an accuracy of +/- 6% for a sample of 200 patients (95% CI: 84% to 96%), and of about 5% for a sample of 400 patients (95% CI: 86% to 94%).

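### The pooled accuracy estimates get plain binomial intervals that assume independent patients; if results vary between the 15 or more centres, these intervals and the stated 2.4% accuracy are too narrow.

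*Protocol*

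**What the plan says.** **Centres and operators.** The synopsis gives the number of centres as "At least 15: the 15 Pilot Units of Coordination in Geriatric Oncology", together with institutions of the oncology network. Step 1 of the synopsis, which includes the G8, is assigned to "Medical oncologists, surgeons, radiotherapists" and others. The reference assessment is assigned to "geriatrician and geriatric assessment nurse for UPCOG". Section 4 records on-site monitoring at 19 sites.

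**Analysis.** Section 3.4.2 runs the main validation on all included patients together. For sensitivity, section 3.4.3 specifies the proportion and its interval: "among the patients having at least one abnormal CGA element. A 95% CI will be reported (binomial distribution". It names the binomial distribution again for specificity and negative predictive value. The synopsis (Hypotheses and statistical analyses) names it for all four accuracy measures. Sections 3.3.2.3 and 3.4.2 break results down by cancer type, stage and therapeutic strategy. Centre enters none of the analyses described.

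**Precision target.** From the exploratory work, section 3.4.1.1 assumes "a sensitivity of about 90%, when we use as gold standard the presence of an abnormal score for at least one questionnaire". For the share of abnormal patients its assumption is "a prevalence of 50% of patients with at least one abnormal questionnaire". With 750 abnormal patients taken as sufficient, the target reads: "estimate the sensitivity with a sufficient accuracy (2.4%) and to obtain a 95% CI between 88% and 92" (limits in percent). The synopsis gives 87.6% to 92.4% for the same accuracy.

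**The concern.** The primary aim is estimation, so the width of the interval is the design target. A binomial interval is valid if the patients' results are independent. Patients in one centre share screeners, a way of grading and a referral pattern. The reference is positive when any one of seven elements is abnormal, so one local habit, for example in grading comorbidity on the CIRS-G, can change who counts as abnormal. If such habits or the case mix differ between centres, results within a centre are correlated and the pooled estimate is less certain than the binomial formula says.

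Two things are at stake: whether the reported 95% intervals cover as stated, and whether a pooled sensitivity near 90% hides centres that miss more patients. The protocol says that missed patients are its main worry.

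**Working it through.** **Inputs from the protocol:** expected sensitivity 90%; 750 patients with an abnormal assessment; at least 15 centres; binomial 95% interval. **Assumed, because the documents do not give it:** the ICC of a positive G8 among abnormal patients, taken from 0 to 0.02, and equal centre sizes.

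**Step 1: reproduce the plan's figure.** The expected count is 0.90 × 750 = 675. The exact (Clopper-Pearson) 95% interval for 675/750 is 87.63% to 92.05%.
- The lower arm is 90 − 87.63 = 2.37 points, which rounds to the stated 2.4%. The limits round to the 88% and 92% of section 3.4.1.1.
- The synopsis upper limit of 92.4% is obtained by adding the lower arm to 90%; the exact upper limit is 92.05%.
- The normal approximation, 1.96 × √(0.9 × 0.1 / 750), gives 2.15 points and does not reproduce 2.4%.

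The stated 2.4% is therefore an exact binomial figure with a design effect of 1, and the comparison below stays on the exact scale.

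**Step 2: allow for centre.** Design effect D = 1 + (m − 1) × ICC, where m is the number of abnormal patients per centre. The effective sample size is 750 / D, and the exact interval is recomputed on it. With 15 centres, m = 750 / 15 = 50. The last column is the approximate coverage of an unadjusted nominal 95% interval, 2Φ(1.96/√D) − 1.

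| ICC | D | Effective n | Exact 95% CI | Lower arm (points) | Coverage if unadjusted |
|---|---|---|---|---|---|
| 0 | 1.00 | 750 | 87.6% to 92.1% | 2.4 | 95% |
| 0.005 | 1.25 | 602 | 87.3% to 92.3% | 2.7 | 92% |
| 0.01 | 1.49 | 503 | 87.0% to 92.5% | 3.0 | 89% |
| 0.02 | 1.98 | 379 | 86.5% to 92.8% | 3.5 | 84% |

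**Step 3: vary the number and size of centres.**
- With 19 equal centres, m = 750 / 19 = 39.5, and the lower arm is 2.6, 2.8 and 3.3 points at ICC 0.005, 0.01 and 0.02.
- With an assumed 30 equal centres, m = 25. At ICC 0.01, D = 1 + 24 × 0.01 = 1.24, about the same as ICC 0.005 with 15 centres, so the lower arm is about 2.7 points.
- With 15 centres of unequal size, assuming a coefficient of variation of 0.7, D at ICC 0.01 becomes 1 + (1.49 × 50 − 1) × 0.01 = 1.73 instead of 1.49.

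**Step 4: what these ICCs mean.** The between-centre standard deviation of sensitivity is √(ICC × 0.9 × 0.1). This is 2.1, 3.0 and 4.2 points at ICC 0.005, 0.01 and 0.02.

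**The case against.** The strongest reply is that no loss of precision has been shown. The ICC is unknown, and at ICC 0 the 2.4% is correct. A reader might infer that the stated precision is wrong as it stands; the documents do not support that. They support only a conditional statement.

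A reader might also infer that using different people for the screening and reference tests narrows the interval. It does not. That separation serves the blinding of the reference assessment and protects against bias; only variation between centres matters here. Nor is operator variation ignored: section 3.3.2.2 plans an oncologist-versus-nurse comparison of the G8, by item and overall. It does not compare centres, however, and it does not cover the reference tests. The reference cut-offs are common to all sites, and some elements leave little room for local habit, such as a timed test and a self-completed depression scale.

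The number of recruiting centres is not settled either. Fifteen is a minimum, and the 19 in section 4 are monitored sites. More centres would reduce the effect.

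The text is also an abridged translation, and the statistical analysis plan is not at hand. An analysis by centre may exist there. That does not remove the point, because the protocol itself names the binomial method.

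Finally, centre-by-centre estimates would be noisy. With 50 abnormal patients the half-width is 1.96 × √(0.09 / 50) = 8.3 points. This stands, so such estimates can only be descriptive.

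**Conclusion.** The point holds in conditional form. The protocol commits to intervals that assume independent patients for data pooled over at least 15 centres, and its stated 2.4% carries the same assumption. Any positive correlation within centres makes both too narrow. For ICCs of 0.005 to 0.02 and 15 to 19 equal centres, the lower arm is about 2.6 to 3.5 points instead of 2.4.

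That is a modest loss, and the estimate stays usable. The protocol sets no pass mark for sensitivity, so no decision rule changes. The size depends wholly on an ICC that the documents do not supply. The documents also do not show that particular centres perform poorly; the planned analyses would simply not reveal it if they did.

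**What to change.** In section 3.4.3 and the matching synopsis text:

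- Beside the binomial intervals, report 95% intervals for sensitivity, specificity and predictive values that allow for clustering by centre, for both G8 and VES-13. Suitable methods are cluster-robust logistic regression or GEE with a small-sample correction, which 15 to 19 clusters call for, or a model with a random centre effect. If the random effect is used, report the value averaged over centres so that it stays comparable with the pooled proportion.
- In section 3.4.1.1 and the synopsis, state that the 2.4% accuracy holds under independence between patients, and give the same interval in both places.
- Show the variation in sensitivity and specificity between centres descriptively, with the number of patients per centre and no formal comparison.

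No extra patients are needed, and the work is a few lines of wording and code, provided that each patient's centre is in the database. The downside is somewhat wider intervals and a slightly less favourable stated precision. If the correlation proves close to zero, the two sets of intervals will nearly agree and the independence assumption will have been checked.

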**Assessment of the predictive validity:**

The G8 and VES-13 predictive validity will be assessed at 1 and 5 years according to the following events: mortality, disease progression, and institutionalisation.

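### Kaplan-Meier curves are planned for institutionalisation with no rule for deaths that come first; if deaths are censored, the absolute five-year risk is overstated

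*Protocol*

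**What the plan says.** In Protocol section 3.3.2.2, predictive validity is to be assessed at 1 and 5 years "according to the following events: mortality, disease progression, and institutionalisation". The analysis is described in the prognostic item of section 3.4.3:

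- **Times:** "delays will be calculated between the origin date (inclusion in the study) and the event date (death, progression, or institutionalisation").
- **Curves:** "Survival curves will be represented graphically with Kaplan-Meier’s method". This is one statement for the whole prognostic analysis.
- **Medians:** "Median times for survival will be reported with a 95% CI".
- **Group comparison:** categories of G8 and VES-13 are compared "thanks to a Log-Rank test, if application conditions are respected".
- **Regression:** a Cox model gives relative risks "for the occurrence of various events of interest (death and institutionalisation), taking into account the durations". Progression is not in that list.
- **Risk set:** "The analysis of the “institutionalisation” risk will be only on the patients not institutionalised at the inclusion (population at risk").

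On follow-up, the synopsis says: "Data collection will be done at 1 and 5 years in order to collect data on vital status, disease progression, lifestyle (ambulatory, institutionalised"). Patients are aged 70 or more, have cancer and are followed for 5 years.

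Competing risks and cumulative incidence are not mentioned anywhere, and neither is the treatment of a death that precedes institutionalisation or progression.

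**The concern.** Institutionalisation is a single-cause endpoint here. It is named separately from death in the Cox model and has its own risk set, so it is not part of a composite. The plan takes care over who is at risk at inclusion, but not over patients who leave the risk set by dying. In cancer patients of this age followed for 5 years, many such deaths must be expected.

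If those deaths are censored, Kaplan-Meier treats the dead as if they could still be institutionalised at the rate seen in survivors. One minus Kaplan-Meier then estimates a risk in a setting without death, which is higher than the proportion of patients who will actually be institutionalised.

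Mortality is itself one of the events that G8 and VES-13 are meant to predict. If they do predict it, the overstatement differs between the very categories being compared, and the absolute risks read off the curves are not comparable on the same footing.

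**Working it through.** **The plan's own figure.** There is none to reproduce. The protocol states no rate, event count, hazard ratio or power for the prognostic analysis. Every rate below is an assumption, and a range is shown.

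**Formulas.** Constant hazards per year, *i* for institutionalisation and *d* for death without institutionalisation, at time *t* in years:

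- Kaplan-Meier with deaths censored: 1 − exp(−*i·t*)
- Cumulative incidence with death competing: *i*/(*i*+*d*) × [1 − exp(−(*i*+*d*)·*t*)]

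The first exceeds the second whenever *d* > 0.

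**Range.** *i* runs from 0.02 to 0.10 per year. *d* is set from a 1-year survival of 95% down to 60%, so *d* = −ln(0.95) = 0.051 up to −ln(0.60) = 0.511.

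| Time | Ratio, 1−KM to cumulative incidence | Absolute overstatement |
|---|---|---|
| 1 year | 1.03 to 1.28 | 0.05 to 2.0 points |
| 5 years | 1.12 to 2.72 | 1.1 to 23.7 points |

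One line in full, at 5 years with *i* = 0.02 and *d* = 0.511: 1 − exp(−0.10) = 9.5%. Cumulative incidence is 0.02/0.531 × [1 − exp(−2.654)] = 3.5%. The ratio from unrounded values is 2.72.

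**Effect on the contrast between categories, at 5 years.**

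*Example A, contrast too large.* Abnormal category: *i* = 0.04, *d* = 0.25. Normal category: *i* = 0.02, *d* = 0.10.
- 1−KM: 1 − exp(−0.20) = 18.1% against 1 − exp(−0.10) = 9.5%, a difference of 8.6 points.
- Cumulative incidence: 0.04/0.29 × [1 − exp(−1.45)] = 10.6% against 0.02/0.12 × [1 − exp(−0.60)] = 7.5%, a difference of 3.0 points (from unrounded values).

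*Example B, contrast too small.* *i* = 0.03 in both; *d* = 0.30 (abnormal) and 0.10 (normal).
- 1−KM: 1 − exp(−0.15) = 13.9% in both, no difference.
- Cumulative incidence: 0.03/0.33 × [1 − exp(−1.65)] = 7.3% against 0.03/0.13 × [1 − exp(−0.65)] = 11.0%. Fewer patients in the abnormal category are institutionalised, because more die first.

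*Example C, equal mortality.* With 1-year survival of 80% and *i* = 0.03 in both categories, the overstatement is the same in each: 5.4 points, ratio 1.64.

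**Log-rank test with deaths censored.** In a simulation of 4,000 runs with 1,500 patients split 1:1, equal institutionalisation hazards and unequal death hazards, the test rejected in 4.9% of runs at a nominal 5%. It holds its size as a test of the cause-specific hazard.

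**Progression, if death is not counted as an event.** Assumed progression hazard 0.2 per year in both categories; death without progression 0.05 against 0.15 per year. At 5 years 1−KM is 63.2% in both, while the cumulative incidence is 57.1% and 47.2%.

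**The case against.** The strongest reply is that censoring at death is inferred, not stated. The document is an abridged translation, an analysis plan may exist, and censoring rules are often left to it. That is fair, and it is why the point is conditional. It does not dispose of it: the protocol itself names the estimator for a single-cause endpoint, and the caveat about application conditions is attached to the log-rank test, not to the curves.

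Several stronger readings are tempting, and the documents do not support them:

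- **That the log-rank and Cox analyses are also biased.** With deaths censored, both validly compare cause-specific hazards. They need that label, since calling the Cox result a relative risk invites an absolute reading. Gray's test and the Fine-Gray model answer a different question.
- **That medians are planned for the non-fatal events.** The sentence on medians speaks of survival only.
- **That progression has the same defect.** It is not among the Cox events listed, and the text does not say whether death counts. If it does, the endpoint is progression-free survival and Kaplan-Meier is valid. What can be said is that the endpoint is undefined.
- **That the bias is worst in patients flagged by G8 and exaggerates its separation.** No mortality figure by category is given. Example B goes the other way. Even with higher mortality in the abnormal category (1-year survival 70% against 90%), institutionalisation hazards of 0.03 (abnormal) and 0.10 (normal) give a larger absolute overstatement in the normal category: 8.1 against 7.3 points.
- **That dates of institutionalisation are not collected.** Section 3.4.3 presupposes event dates, and the follow-up form is not shown. Two contact times alone do not show that dates are missing.

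**Conclusion.** The point holds in limited form. The protocol fixes Kaplan-Meier for time to institutionalisation and leaves open how a prior death is treated. If deaths are censored, the absolute probability of institutionalisation is overstated. The direction follows from the method alone; the size rests on assumed constant hazards. Over the range examined, the 1-year analysis is little affected, and the 5-year analysis is where the choice matters. Any distortion of the contrast between categories depends on a mortality difference that the documents do not quantify, and its direction cannot be settled in advance.

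Predictive validity is a secondary objective. The main validation against the geriatric assessment does not use these curves. The change is worth making because it is cheap and improves a method that the plan names.

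**What to change.** Revise the prognostic item of section 3.4.3 as follows.

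1. Keep Kaplan-Meier, log-rank and Cox for death.
2. For institutionalisation, replace the Kaplan-Meier curve with the cumulative incidence (Aalen-Johansen estimator), with death as a competing event, by G8 and VES-13 category at 1 and 5 years.
3. Keep log-rank and Cox for institutionalisation, state that deaths are censored, label the results cause-specific, and show them beside the results for death. Gray's test or a Fine-Gray model is an optional complement if absolute risk is of interest.
4. For progression, state whether death counts as an event. If so, call it progression-free survival and keep Kaplan-Meier. If not, use cumulative incidence there too.

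The cost is a few sentences of wording and slightly more analysis work with standard methods. Reported absolute risks of institutionalisation will be lower than Kaplan-Meier would give, and the report should explain why.
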